## Discussion

Moderate to severe acute post-partum anaemia is associated with a number of short and long-term adverse health outcomes hence active treatment is necessary and is commonly indicated by a combination of haemoglobin and iron deficit and symptom severity. Whilst RBC transfusion is the mainstay treatment for severe symptomatic anaemia, wide practice variations exist in the management of mild-moderate anaemia in otherwise clinically stable women. If over treated with blood products, these women are placed at risk of transfusion related adverse effects, which although uncommon, can be life threatening and are almost always associated with ongoing morbidity.

The argument supporting expectant management for these patients has been well outlined in recent studies though there is no standard definition of what expectant management entails. Some institutes advocate the use of oral iron only whilst others prescribe parenteral replacement. Long term data indicates that parenteral iron is faster and more effective than oral iron at restoring haemoglobin and total body iron deficits and has the added advantage of avoiding gastrointestinal side effects which often interrupt compliance in the post-natal cohort [2, 3, 24]. Moreover, the lag period to replenish iron stores and induce erythropoeisis is significantly contracted with IV compared to oral therapy. This, coupled with an attractive safety and tolerance profile as well as being cheaper and more available, introduces parenteral iron as an appropriate alternative to blood transfusions in selected women.

If our study hypotheses are true then intravenous iron presents as a safer, sustained and more cost-effective alternative to blood transfusion in the management of hemodynamically stable women with acute post-partum anaemia. Our findings will be particularly useful for patients ineligible for treatment with blood products due to clinical or religious reasons and in under-resourced settings both within Australia and internationally. Ultimately we would hope these findings support the widespread implementation of parenteral iron into routine post-natal practice policies in an effort to improve patient safety and minimise resource wastage.

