### Primary objectives

To determine if intravenous iron is non-inferior to RBC transfusion in correcting haemoglobin deficit, replenishing iron stores and improving clinical symptoms in women with acute post-partum anaemia without increasing the rate of adverse outcomes.

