### Secondary objectives

To determine if intravenous iron is superior to RBC transfusion in improving the quality of breast-feeding in women with acute post-partum anaemia.

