### Hypothesis

Intravenous iron is non-inferior to RBC transfusion in women with acute post partum anaemia in correcting Hb levels and improving clinical symptoms with no increased rate of adverse outcomes.

Intravenous iron is superior to blood transfusion in replenishing pre-pregnancy iron stores.

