### Outcomes

#### Primary outcomes

Hb, ferritn and CRP levels at Day 7

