### Data collection

Each participant will have a study file labelled with their name, medical record number, study identification number and allocated treatment. This will contain copies of their consent forms (the original will remain in their hospital file while they are an inpatient), questionnaires and comprehensive study checklists template for documenting outcome variables and other clinical data. Files will be kept in locked cabinets on the ward and in the principle researcher’s office after discharge and remain on site for 7 years before being destroyed/archived.

Baseline blood results (Hb, ferritin, CRP) for all enrolled participants will be manually transcribed by researchers from the hospital electronic database into the participant’s study file. Once allocated to an intervention, the number and coding sticker of each blood unit or the serial number and dose of the pre-packaged iron infusion will be recorded in the template.

Patient symptoms will be scored on Day 0 prior to receiving any intervention using previously validated HRQoL questionnaires: the EuroQol-5D (E-5D), the Multidimensional Fatigue Inventory (MFI-20) and our in-hospital devised Post-Partum Symptom Score (PPSS).

The EQ-5D measures a patient’s activity level and emotional attitude at a single point in time, indirectly reflecting symptom severity. It consists of five items (Mobility, Self-Care, Usual Activities, Pain/Discomfort and Anxiety/Depression) where a patient scores: 1 = no problems, 2 = more problems, 3 = extreme problems. The sixth item is a patient’s own global evaluation of their health using a visual analogue scale with a range from 0 (worst imaginable health state) to 100 (best imaginable health state) [21].

The MFI is a 20-item self-report instrument designed to comprehensively measure fatigue. It evaluates: general, physical and mental fatigue and reduced motivation and activity. Patients score each dimension on a scale ranging from 4 to 20 where 4 is optimal. Hence, higher scores indicate more severe symptoms. Scales are balanced to reduce the influence of response tendencies. Each scale sub-total is interpreted independently. Questions are structured to evaluate symptoms over a period of time (5-7 days) which is particularly useful to measure treatment impacts [22]. Both the MFI and EQ-5D have previously been validated in pilot studies of obstetric cohorts [23].

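### The Discussion says that meeting the hypotheses makes intravenous iron 'safer' and 'more cost-effective', but the hypotheses ask only that harms not rise, and no cost outcome is named

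*Protocol article*

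**What the plan says.** The closing part of the Discussion makes the trial's hypotheses the condition for a three-part conclusion: "If our study hypotheses are true then intravenous iron presents as a safer, sustained and more cost-effective alternative to blood transfusion".

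The Hypothesis section has two parts. The first is non-inferiority of iron "in correcting Hb levels and improving clinical symptoms with no increased rate of adverse outcomes". The second is "Intravenous iron is superior to blood transfusion in replenishing pre-pregnancy iron stores". The primary objective words its safety element in the same way as the first hypothesis: "without increasing the rate of adverse outcomes". The only superiority objective among the stated objectives concerns feeding: "To determine if intravenous iron is superior to RBC transfusion in improving the quality of breast-feeding".

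The primary outcomes are "Hb, ferritn and CRP levels at Day 7". The secondary outcomes are later laboratory values, clinical symptoms, breastfeeding quality and adverse reactions. The Statistics section plans rates with 95% confidence intervals for adverse reactions and states no superiority comparison for them.

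The abstract's Discussion paragraph takes a similar step. Equivalence, including on safety endpoints, is said to open the way for iron as the preferred option, in order to reduce transfusion reactions and costs.

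**The concern.** 'Safer' is a claim of fewer or less serious harms. 'More cost-effective' is a claim about costs set against effects. The sentence says both follow once the hypotheses are shown to be true, yet the safety hypothesis is met when the arms are equally safe, and nothing in the hypotheses concerns cost.

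The wording fixes in advance what a successful trial will be taken to mean. The same Discussion paragraph hopes that the findings will support broad adoption of parenteral iron in routine postnatal policy. A trial that found equal harm and made no cost comparison could then be summarised, in line with its own published protocol, as having shown iron to be safer and better value.

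**Working it through.** No arithmetic applies: the Discussion sentence contains no figure to reproduce. The check is whether each label follows from the hypotheses, taking every hypothesis as proven.

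**What the hypotheses supply** (Hypothesis section)
1. Haemoglobin correction: non-inferior.
2. Clinical symptoms: non-inferior.
3. Adverse outcomes: rate not increased.
4. Iron stores: superior.

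**What the Discussion concludes, label by label**

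| Label | What it would need | What the protocol supplies | Does it follow? |
|---|---|---|---|
| Safer | Fewer adverse outcomes on iron than on transfusion | Item 3 only. The primary objective is worded the same way, and no superiority comparison is stated in Statistics | No |
| Sustained | An effect lasting beyond the early period | Item 4, with haemoglobin, ferritin and reticulocytes at Days 14 and 28 among the secondary outcomes | Has support; not part of this point |
| More cost-effective | A comparison of costs in relation to effects | No cost, resource-use or cost-effectiveness item in the objectives, hypotheses, outcomes or Statistics | No |

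**Safer.** Let the risk difference be the adverse-outcome rate on iron minus the rate on transfusion. The hypothesis is that this difference is not above zero. 'Safer' requires it to be below zero. A difference of exactly zero satisfies the first and contradicts the second. One case is enough to break the inference, and it does so at any sample size.

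**More cost-effective.** None of the four items contains a cost term, so the four can all be true whatever the costs turn out to be. The Data collection section says that "the number and coding sticker of each blood unit or the serial number and dose of the pre-packaged iron infusion will be recorded", and EQ-5D is collected, but these are records of treatment given and health status. No outcome or analysis turns them into a cost comparison.

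**Could background statements fill the gap?** The Background describes newer iron preparations as cheap and as having a milder side-effect profile than transfusion, and the Discussion calls parenteral iron cheaper and more available. These are premises brought to the trial. The sentence at issue makes the trial's hypotheses the condition, and proving those hypotheses neither confirms nor refutes the premises.

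**The case against.** The strongest reply is that this is one forward-looking sentence in a Discussion. It does not appear under Hypothesis, Outcomes or Statistics, and no test, margin or stopping step refers to it. The surrounding language is hedged: the authors hope for adoption, and the abstract says only that iron may become preferred. Adverse-reaction rates will be reported with confidence intervals, so readers would see an equal-harm result. The authors may also be reasoning that, given similar effects and a lower price known beforehand, iron is the economical choice.

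Much of this stands, and it limits the point to wording. It does not rescue the two labels, because the sentence attributes them to the hypotheses and not to prior evidence. If prior evidence is meant, the text should say so. An analysis plan could not close the gap either, since no analysis makes 'not increased' mean 'reduced'.

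Several stronger readings might be inferred, and the protocol does not support them:
- **A formal decision rule.** The sentence has an if-then form, but nothing in the analysis depends on it.
- **'Sustained' is equally unfounded.** The iron-store hypothesis and the Day 14 and Day 28 measurements give it some basis.
- **A calculable chance of wrongly declaring iron safer.** The protocol gives no expected event rates for the two arms and no criterion for judging that harms have not increased. Any such figure would rest on assumptions and would cover only one of the four conditions.
- **A cost-effectiveness analysis is already available from recorded data.** Blood units, iron dose and EQ-5D are recorded, but no unit costs are listed.

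**Conclusion.** The point holds for 'safer' and 'more cost-effective'. Neither follows from the stated hypotheses, even if all are proven: equal harm rates satisfy the safety hypothesis, and cost appears in no hypothesis, outcome or analysis.

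The size is minor. Two of the three labels in one Discussion sentence are affected, together with the matching step in the abstract. Conduct, sample size and the primary haemoglobin analysis are untouched. The conclusion depends only on the wording of the protocol article and on reading 'safer' as fewer harms. It needs no assumption about event rates.

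**What to change.** 1. **Reword the Discussion sentence**, and bring the abstract's Discussion paragraph into line. If the hypotheses are met, the conclusion should be that iron is non-inferior to transfusion for haemoglobin and symptoms, with no demonstrated increase in adverse outcomes, and superior in replenishing iron stores.
2. **Give 'safer' its own condition.** Use the word only if the 95% confidence interval for the risk difference in adverse outcomes (iron minus transfusion) lies wholly below zero. Otherwise report the difference with its interval and leave the word out.
3. **Delete 'more cost-effective'**, or attribute any lower price explicitly to prior evidence and not to this trial.

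The cost is a few changed sentences and one interval computed from adverse-event counts that the trial already plans to report. No extra participants, visits or data are needed. The downside is a more modest permitted claim if the safety interval includes zero.

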## Abbreviations

BP: Blood pressure
CRP: C-Reactive Protein
Hb: Haemoglobin
HR: Heart rate
HRQoL: Health related quality of life
IV: Intravenous
PPH: Primary post-partum haemorrhage
RBC: Red blood cell
RR: Respiratory rate
